### Randomised controlled trial

Using an RCT methodology we will compare a ‘care-as-usual’ (CaU) group with an intervention group. Both groups will complete parental mental health, psychosocial needs, and child developmental screeners via WMG-E. Furthermore, both groups, if risk is identified, will receive electronic resources guiding them to health services that can be accessed for more detailed assessments.

The intervention group will be provided with ongoing monitoring, via a service navigator, to ensure uptake of recommendations and access to additional support for those identified to be at risk. The service navigator will first triage intervention families based on their level of risk as indicated by the WMG-E platform which screens for developmental, parental mental health, and psychosocial risk. Participants who indicate no developmental concerns on the LTSAE and psychosocial concerns on the WE CARE questionnaire [17] and have scores lower than 20 on the Kessler Psychological Distress (K10) scale [18] will be considered low risk. Participants who indicate one or more developmental and/or psychosocial concerns and/or have scores ranging from 20 to 24 on the K10 will be considered medium risk. Participants who have scores equal to or greater than 25 on the K10 and/or indicate risks of homelessness, domestic violence, loss of electricity, or food insecurity will be considered high risk. Completing the screening tools on the WMG-E platform will take between 10 and 15 min.

Families with lower level risks will be connected with local services and might also be provided with information on online resources (e.g., free to access online parenting programs such as ParentWorks [19] or Movember Family Man [20]) or therapist-assisted interventions (e.g., online or in-person Parent-Child Interaction Therapy [21]). For families who are at high risk, in addition to receiving resources and linkages to services as mentioned above, they will receive in-person assessments (through a KIDS-Connect hub [22] with capacity to reach families at homes or other community facilities) to determine the complexity of health needs followed by appropriate referrals and a ‘warm hand-over’ (i.e., directly linking patients to services in a supportive manner) to recommended services. The duration of in-person (or digital as indicated in extreme circumstances) assessments will depend on the needs identified by the WMG-E, however, these assessments generally range from 30 to 60 min [22]. Once the in-person assessment is completed and families are linked with recommended services, the type and duration of services they receive will depend on their needs. For example, families with psychological needs may receive ten 60-min sessions with a psychologist while families with unmet psychosocial needs who access services such as Uniting (community service agency) [22, 23] may receive 2–3 sessions targeted at addressing psychosocial needs. Furthermore, these families will receive follow-up support by the navigator to ensure engagement with recommended services and continuity of care. Follow-ups will occur fortnightly via telephone for a duration of 10 to 20 min.

We hypothesise that in the first 6 months, the intervention group will have better access and engagement with services due to this group not only getting linked up with services but also continuity of care through the service navigator to ensure the uptake of recommended services. Further we hypothesize that, families in the intervention group that are connected with services will also show a significantly greater increase in wellbeing relative to the control group, at the 12 month follow up. This is because, via the service navigator, they will have assistance in connecting with services and ongoing monitoring and support to ensure that their needs are being met.

### Implementation evaluation

The implementation evaluation will involve semi-structured interviews conducted with participants and stakeholders (e.g., service providers, policy makers) to clarify their experiences with the WMG-E platform and the service navigator, and to identify facilitators and barriers to intervention success. Specifically, the interviews will consider experiences with using the WMG-E app and the service navigator, perceived feasibility and benefits, ways to improve the WMG-E platform and user experience, and differences between routine clinic-based health services and community-based approaches to services.

## Methods

### Phase 1: randomised controlled trial

#### Design

The study design is a two (group: intervention versus control) by three (time: baseline [Time 1], post-assessment [Time 2], and follow-up [Time 3]) RCT.

#### Participants

Participants will include 300 parents/caregivers (150 from Fairfield Local Government Area (LGA) and 150 from Murrumbidgee Local Health District (LHD)) of children aged 6 months to 3 years (inclusive).

#### Setting

Fairfield (population: 198,817; 102 km^2^) [24] is an urban area and has a high proportion of CALD families, with about 70% of residents speaking a language other than English at home [24]. Murrumbidgee LHD (population: 77,652; 125,242 km^2^) [24] is considered mostly regional with one remote area making access to health care a challenge for most families with young children.

#### Procedure

##### Recruitment

Families attending child and family health services, refugee health services, supported playgroups, parenting groups, NGO services, GP clinics, special paediatric clinics, or Child and Family Health Nurse services in Murrumbidgee LHD and Fairfield LGA will be informed about the study by their service provider. They will also be provided with a quick response (QR) code with a hyperlink to the WMG-E app which they can access using tablet devices provided by the service they are attending or using a personal smartphone. Families will be excluded from the research if they are allocated to the control group but are in “acute crisis” based on their questionnaire responses (i.e., K10 > 25 and/or risk of homelessness, domestic violence, loss of electricity, or no food). These families will automatically be considered RCT dropouts and will be contacted by a researcher who will assist them in engaging with services.

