##### Randomisation

Upon completion of the consent forms and Time 1 questionnaires, families will be randomised to either the intervention or CaU group. Computerized randomisation software will be used to create a randomisation table via REDCap (a secure web application for building and managing online surveys and databases) [25]. Participants will be assigned randomly to each arm ensuring a 50:50 ratio.

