##### Parent psychosocial needs

Parent psychosocial needs will be assessed using the WE CARE questionnaire [17]. The questionnaire consists of six (yes/no) items querying psychosocial needs: childcare, employment, homelessness, food security, education, and utilities. The measure also includes follow-up questions that appear if participants indicate “yes” to any of the six items. These items will be summed up to create a score out of 6. These follow-up questionnaires require participants to answer on a three-point scale (yes, no, or maybe later), whether they require additional support for addressing their unmet psychosocial need/s. The measure has good psychometric properties, including excellent test-retest reliability (r. = 0.92) [17].

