##### Statistical analysis

A multilevel models estimated by restricted maximum likelihood (REML) with logit link function will be used to model service utilisation over the 3 time points. The main predictors of interest will be time, group and a time by group interaction which will compare service utilization between the groups at each time point. The analysis will be adjusted for the caregivers, socioeconomic status, and the main language spoken in the home.

A multilevel model estimated by restricted maximum likelihood (REML) with identity link function will be used to model the K10, WE CARE and LTSAE totals. The main predictors of interest are time, group and time by group interaction. The analysis will be adjusted for the caregivers, socioeconomic status, and the main language spoken in the home.

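### Acute-crisis families are removed after allocation and from the control arm only, so the arms differ on Time 1 risk and high-risk families have almost no randomised comparator

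*Protocol article*

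**What the plan says.** The Recruitment section of the protocol article states: "Families will be excluded from the research if they are allocated to the control group but are in" acute crisis. It defines this as a K10 score above 25, or any of four social emergencies (housing, family violence, power cut off, no food). It adds: "These families will automatically be considered RCT dropouts and will be contacted by a researcher who will assist them in engaging with services".

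The Randomisation section fixes the order of events: "Upon completion of the consent forms and Time 1 questionnaires, families will be randomised to either the intervention or CaU group".

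The Randomised controlled trial section under Objectives places a family in the high-risk tier for "scores equal to or greater than 25 on the K10 and/or indicate risks of homelessness, domestic violence, loss of electricity, or food insecurity". Such families in the intervention arm are retained: "For families who are at high risk, in addition to receiving resources and linkages to services as mentioned above, they will receive in-person assessments". The only dropout rule for that arm, in the Intervention group section, concerns failure to engage with the navigator, not crisis status.

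The wellbeing hypothesis is that connected intervention families "will also show a significantly greater increase in wellbeing relative to the control group, at the 12 month follow up". K10 and the WE CARE total are both modelled outcomes. WE CARE has six "items querying psychosocial needs: childcare, employment, homelessness, food security, education, and utilities". On covariates, the Statistical analysis section says: "The analysis will be adjusted for the caregivers, socioeconomic status, and the main language spoken in the home". No measure of Time 1 risk is named.

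**The concern.** Randomisation makes the arms alike in expectation, and that protection is lost if families are then removed from one arm because of a prognostic baseline characteristic. Here the characteristic is severe distress or acute social need, and it is removed from controls only.

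Two things are at stake. First, the exclusion criteria nearly coincide with the high-risk tier, so the families who receive the most intensive form of the package have almost no counterparts in the control arm. No covariate can restore a stratum that is absent. The Background says the study will test the navigator in families that the platform flags as high risk. If that phrase means the tier, this aim loses its comparison. Second, the rule selects controls on K10 and on some WE CARE items, which are themselves analysed outcomes. Controls chosen for low Time 1 scores will tend to drift up, intervention families will not, and a difference in change would read this as navigator benefit.

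**Working it through.** **The plan's own figure.** With 122 per arm, 30% against 60% and two-sided 5%, power is 0.998, so the stated power above 99% reproduces.

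**The two definitions side by side.** The tier uses K10 of at least 25 and food insecurity; the exclusion uses K10 above 25 and no food. On the text, the high-risk controls who remain are those with K10 of exactly 25 and no crisis item, and those with food insecurity short of no food.

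**Counts.** The document gives no crisis share. Assume the tier is 10%, 20% or 30% of 150 per arm, and that 10% or 30% of it escapes the exclusion (halves rounded up):

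| Tier share | High-risk intervention | High-risk controls left (10% / 30% escape) | Controls removed |
|---|---|---|---|
| 10% | 15 | 2 / 5 | 13 / 10 |
| 20% | 30 | 3 / 9 | 27 / 21 |
| 30% | 45 | 5 / 14 | 40 / 31 |

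The intervention counts are upper limits, because the navigator non-engagement rule may drop some. The removed share r runs from 0.10 × 0.70 = 0.07 to 0.30 × 0.90 = 0.27.

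**K10.** Assume all removals are through K10, scores are normal, and the correlation between visits is ρ = 0.5 to 0.7.
- Removing the top share r lowers the control Time 1 mean by φ(z)/(1 − r) SD, with z the upper-r cut-point: 0.144 SD at r = 0.07 and 0.453 SD at r = 0.27.
- With no navigator effect, the later control rise is (1 − ρ) × gap: 0.3 × 0.144 = 0.043 SD to 0.5 × 0.453 = 0.226 SD.
- A random-intercept model with time by group, simulated with 1,000,000 per arm, gives 0.04 to 0.23 SD when the removed families' rows are deleted and 0.00 when their Time 1 rows stay in.
- The effect is smaller if removals are mostly through the social items.

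**WE CARE.** Suppose three items (homelessness, food security, utilities) were emptied completely in controls at Time 1, with prevalence p per item (assumed 3% to 10%) and persistence s (assumed 50% to 70%). The later rise would be 3p(1 − s)/(1 − p): 0.028 items (p = 0.03, s = 0.7) to 0.167 items (p = 0.10, s = 0.5), out of 6. The exclusion is narrower than these items, because no food and loss of electricity are the extreme forms of food and utility need. The bias is therefore below these figures.

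**Service utilisation.** The Statistical analysis section says the interaction compares the groups at each time point. Treat the exclusion as complete, with crisis share q and no true effect. The false difference is q × (rate in crisis families − rate in others).
- At an assumed 50% against 30%: 2 points at q = 10% and 6 points at q = 30%, with type I error of 6.5% and 17.0%.
- At an assumed 20% against 30%: −1 to −3 points, against the intervention.

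If the interaction is instead read as a difference in change, a stable gap drops out and bias requires different change in crisis families.

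**Power.** For 30% against 60% with 150 against 110, power is 0.998.

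**The case against.** The strongest points on the other side are these.

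- *Families in crisis must be helped.* This stands, but help does not require exclusion: the plan already provides a researcher to assist them.
- *The rule calls them dropouts, and a dropout's Time 1 row normally stays in a REML multilevel model.* This stands in part. The text says both that they are excluded from the research and that they count as dropouts, and an SAP that is not shown may settle which rows enter. The K10 bias must therefore start at 0. Keeping the rows does not restore a high-risk comparator.
- *In-person assessment is not a separate trial question.* This stands. A reader might infer that the trial claims to isolate its effect. The Objectives do not, and the Limitations already say that the contributions of the navigator and the services attended will be hard to separate. The Abstract also describes in-person assessment for the intervention group generally. The point is about high-risk families having almost no comparator, not about a failed test of one component.
- *The sizes rest on assumptions.* They do: crisis share, escape share, correlation, prevalence and persistence are all assumed. The K10 and WE CARE upper ends also cannot occur together, since each puts nearly all removals through its own route. The asymmetry itself needs none of these assumptions.

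**Conclusion.** The point holds. The protocol fixes a post-allocation, control-only exclusion on answers known before randomisation, and nothing elsewhere in the article repairs it. The arms are not comparable on Time 1 risk, and high-risk families have almost no randomised comparator: 15 to 45 intervention families against 2 to 14 controls on the assumed shares.

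The bias is less certain than the structure. For K10, the false time-by-group benefit runs from 0 SD (Time 1 rows kept) to about 0.23 SD (rows removed, 27% of controls removed, correlation 0.5). It points towards the 12-month wellbeing hypothesis, and K10 also supplies the utilities in the Economic analysis. WE CARE is biased in the same direction by less than 0.03 to 0.17 items. Service utilisation, compared at each time point, is biased if crisis families use services at a different rate, in a direction the documents do not fix.

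A reader might also infer that the whole comparison is lost or underpowered. The document does not support that: families below the high-risk tier remain in both arms, and power for the planned difference stays above 99%.

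**What to change.** **Preferred.** Keep crisis controls in the trial with the researcher assistance already planned, invite them to Time 2 and Time 3, and analyse them as allocated. Describe the high-risk contrast as navigator versus researcher assistance.

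The cost is follow-up of about 10 to 40 more controls (assumed shares) and a probably smaller high-risk contrast. The whole-trial comparison survives. With crisis shares of 10% to 30% and 122 per arm:
- If assistance lifts crisis controls from 30% to an assumed 45%, the control rate is 0.9 × 30 + 0.1 × 45 = 31.5% to 0.7 × 30 + 0.3 × 45 = 34.5%. The difference is 28.5 to 25.5 points and power is 0.995 to 0.980.
- If it lifts them to an assumed 60%, the control rate is 33% to 39%, the difference 27 to 21 points, and power 0.989 to 0.907.

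**Alternative, if keeping them as controls is unacceptable.** Apply the same Time 1 crisis criteria to both arms before randomisation, offer those families the navigator outside the RCT, and limit the conclusions to families not in crisis. On the assumed shares, randomising 300 needs 300/0.93 = 323 to 300/0.73 = 411 families screened with the Recruitment criteria, or 300/0.90 = 334 to 300/0.70 = 429 with the high-risk tier criteria (rounded up).

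**In either case**, use one K10 cut-off and one food criterion in the Recruitment section and the risk-tier definition. This costs nothing.

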##### Care-as-usual group

Participants allocated to the CaU will complete Time 1 questionnaires and, if indicated, will also receive a message that their responses to the questionnaires suggest developmental, psychological, and/or psychosocial risk and to seek assistance from local services/organisations. They will then be invited via email to complete Time 2 and Time 3 questionnaires. The control group will not have a service navigator and will not receive continuity of care and support.

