##### Parent mental Health

Parent psychological distress will be assessed using the Kessler Psychological Distress (K10) scale [18] – a ten-item measure. Using a five-point Likert scale, parents are required to indicate how often they have experienced symptoms of depression and anxiety as well as somatic symptoms over the past 4 weeks. One indicates ‘none of the time’ and five, ‘all of the time’. Each item score is combined to calculate the total score. Scores of 20 to 24 (inclusive) indicate mild psychological distress, 25 to 29 (inclusive) indicate moderate psychological distress, and 30 to 50 (inclusive) indicate severe psychological distress. The K-10 has good validity and reliability in various settings and populations [26–28].

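### The control-arm contact rule starts at K10 above 25, while high risk starts at 25, so a control parent scoring exactly 25 falls between the two rules

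*Protocol article*

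**What the plan says.** The article fixes a K10 boundary near 25 in three places.

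- **Randomised controlled trial** (triage by the service navigator). Medium risk applies to those who "have scores ranging from 20 to 24 on the K10 will be considered medium risk". High risk applies to those with "scores equal to or greater than 25 on the K10 and/or indicate risks of homelessness, domestic violence, loss of electricity, or food insecurity".
- **Parent mental Health** (Measures). "Scores of 20 to 24 (inclusive) indicate mild psychological distress, 25 to 29 (inclusive) indicate moderate psychological distress".
- **Recruitment** (control arm). Acute crisis is defined as "K10 > 25 and/or risk of homelessness, domestic violence, loss of electricity, or no food". The consequence is that "These families will automatically be considered RCT dropouts and will be contacted by a researcher who will assist them in engaging with services".

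Two further statements settle what each side of the boundary receives. In the intervention arm, "For families who are at high risk, in addition to receiving resources and linkages to services as mentioned above, they will receive in-person assessments". In the control arm, the Care-as-usual group section says that participants whose answers indicate risk "will also receive a message that their responses to the questionnaires suggest developmental, psychological, and/or psychosocial risk and to seek assistance from local services/organisations"; it gives them no navigator and no continuity of care.

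**The concern.** The risk triage and the distress bands agree that a score of 25 opens the upper category. The Recruitment rule alone puts 25 below the line. It lists almost the same triggers as the high-risk definition, in the same order, so it reads as a restatement in which one comparison sign has changed. No reason is given for a cut one point inside a band.

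The rule is acted on. It is the only place where the article gives a distressed control family contact with a person, and it also decides whether that family stays in the trial. If it is programmed as printed, a control parent whom the plan calls high risk misses the contact given to a parent one point higher. An unclear boundary can also be set up one way in the data system and reported another way.

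**Working it through.** There is no stated figure to reproduce. The check is an enumeration, followed by a rough sizing.

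**1. Where the rules disagree.** The K10 has ten items scored 1 to 5 (Parent mental Health), so totals are the 41 whole numbers from 10 to 50.

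| K10 total | Triage | Distress band | Control rule as printed |
|---|---|---|---|
| 20 to 24 | medium, on K10 alone | mild | no contact on K10 |
| 25 | high | moderate | no contact on K10 |
| 26 to 29 | high | moderate | contact and removal |
| 30 to 50 | high | severe | contact and removal |

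Totals below 20 meet neither rule. Comparing K10 ≥ 25 with K10 > 25 over all 41 totals gives one discordant score, 25. With ≥ 25 in both rules there is none.

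**2. Who is affected.** Control families at exactly 25 with none of the listed social triggers. A family at 25 that does have such a trigger is contacted anyway.

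**3. How many.** The article gives no K10 distribution, so this step rests on assumptions. Take K10 as 10 plus a rounded gamma variable, truncated at 50, with three mean/SD pairs, and 150 controls (Sample size calculations). The count is 150 × P(K10 = 25).

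| Assumed mean/SD | P(K10 = 25) | Families of 150 |
|---|---|---|
| 15/5 | 0.0100 | 1.5 |
| 18.4/6.8 | 0.0228 | 3.4 |
| 22/8 | 0.0364 | 5.5 |

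These counts ignore social triggers, so they are upper values for each distribution. If 40% of those at 25 also had a social trigger (again assumed), multiplying by 0.6 gives 0.9, 2.1 and 3.3.

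**4. Effect of contacting them and keeping them.** Suppose every contacted non-user becomes a service user. With the planning value of 30% current use, the non-user share is 0.7, and the rise in control service use is count × 0.7 / 150:

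- 1.5 × 0.7 / 150 = 0.7 percentage points
- 3.4 × 0.7 / 150 = 1.6 percentage points
- 5.5 × 0.7 / 150 = 2.6 percentage points

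The denominator here is all 150 randomised controls. The existing rule already removes controls above 25: about 7, 20 and 39 of 150 on K10 alone under the same three distributions. Over the 143, 130 and 111 who remain, the same counts give 1.5 × 0.7 / 143 = 0.7, 3.4 × 0.7 / 130 = 1.8 and 5.5 × 0.7 / 111 = 3.5 points. The planned difference is 60% − 30% = 30 points.

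**The case against.** The strongest reply is that the two rules carry different labels and do different jobs. High risk sets how intensively the navigator works; acute crisis removes a control family from the research. The article never says that the two sets must coincide, a condensed article may leave the reason for a narrower rule to the full protocol, and the flow figures, which may print a cut-off, are not available here. This stands in part: a deliberate difference cannot be ruled out. But the near-identical trigger list points to a slip, and a deliberately stricter rule would more naturally start at a band limit such as 30, where severe distress begins. Two explicit cut-offs in one document that disagree are not an omission that article format explains.

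Three stronger readings are tempting and are not supported.

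- A reader might infer that the control rule is also narrower on food, because one section speaks of having no food and the other of food insecurity. The Measures section describes a single yes/no food-security item in WE CARE, so both wordings most plausibly refer to the same answer.
- A reader might infer that a control family at 25 is left with nothing. It still receives the automated message; what it lacks is the researcher's contact.
- A reader might object that intervention families at 25 receive in-person assessment and controls do not. That difference is the contrast under test and is no fault.

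One further objection stands in full. Randomisation follows the Time 1 questionnaires, so the Recruitment rule removes families after allocation and from one arm only. Moving the cut-off to 25 with removal still attached would make that worse, and the fix must avoid it.

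**Conclusion.** Minor, but wrong as written. That the rules disagree at exactly one score follows from the text and needs no assumption. That the disagreement is a slip is a judgement from the parallel wording.

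The number of families is small and cannot be computed from the article. The range of about 1 to 6 of 150 controls depends on the assumed K10 shape, means and SDs, and takes no account of social triggers, which would lower it. No claim is made about sample size or power: a comparison of 150 with 150 would not describe the arms analysed, because the existing rule already removes controls above 25.

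**What to change.** In Recruitment, set the trigger for researcher contact to K10 ≥ 25, matching the high-risk definition. State that control families at exactly 25 with no listed social trigger are contacted but stay in follow-up and in the analysis, so that the one-arm removal after randomisation is not enlarged. If the cut above 25 is intended, give the reason in one sentence.

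The change costs a one-line amendment and one trigger condition in REDCap. Its price is a slight dilution of the contrast, since some contacted controls may take up services: under the assumptions above, at most about 2.6 percentage points over all 150 controls, or 3.5 over those who remain, against a planned 30. That extreme needs the highest assumed distribution, no social triggers among those at 25, and every contacted non-user becoming a user.
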